#### 4.5 Follow-up visits

The study will also include 2 follow-up phone calls: 6, and 12 months. Survey data will be collected over the phone. These phone calls will be audio recorded for data integrity and quality assurance. We will randomly select phone call audio recordings to ensure that they are following our study protocol. Audio recordings will be password protected and stored on the NYU Langone shared drive which is only accessible to our study team members. We will destroy the recordings in July 2029, one year after our grant ends. We will abstract the HbA1c testing results from the medical record at the participant's doctors' offices. Given the missing data issue of the EHR record, we will also use the A1CNow Self Check Device (PTS Diagnostics, Whitestown, IN) to collect participants' most recent HbA1c value. The A1CNow Self Check Device is only utilized for research purposes and may not be used or relied upon as a diagnostic tool. Any concerning results will be shared immediately with their healthcare provider if the healthcare provider is unaware. Our research team has no affiliation with PTS Diagnostics.

[figure not shown]

Figure1. Study Variables

**Primary & Secondary Outcomes Primary outcome: HbA1c:** As part of the usual care, patients with T2D receive a HbA1c blood test at their doctors' office every 3-6 months. we will abstract the HbA1c testing results from the medical record at the participant's health care facility. Once we obtain the consent from participants, we will contact their doctors' offices for HbA1c results. Given the missing data issue of the EHR record, we will also use the A1CNow Self Check Device (PTS Diagnostics, Whitestown, IN) to collect participants' most recent HbA1c value. The procedures are similar to the blood glucose finger prick that participants perform at home. Our trained study staff will guide the participants during this process. The A1CNow Self Check Device is only utilized for research purposes and may not be used or relied upon as a diagnostic tool.

**Secondary outcomes:** Consistent with DSMES programs (Figure 1), we will measure self-efficacy, diabetes self-management behaviors, dietary intake, physical activities, and medication taking at each time points (baseline, 6-, 12-months). All of these surveys have been used and validated in our prior and current studies with Chinese immigrants31,35,3>.

1. **Self-efficacy:** We will use the well-validated Stanford Self-Efficacy for Diabetes Scale3> to measure participants' confidence to manage T2D. This instrument contains 8 items and asks participants to rate their confidence level in performing specific self-management behaviors, using 10-point Likert scale ranging from 1 (not at all confident) to 10 (totally confident). This

instrument has been widely tested and has demonstrated excellent psychometric properties in Chinese immigrants.

2. **Diabetes Self-Management Behaviors:** We will use the Summary of Diabetes Self-Care Activities (SDSCA) to assess participants' adherence to diabetes self-management behaviors. This scale consists of 11 core items and asks participants to describe adherence to diabetes self-care activities over the past 7 days. The reliability and validity of this scale has been well established in Chinese immigrants.
3. **Dietary Intake:** Informed by a previous study and our own studies in Chinese Americans, we will use the 8-item Starting the Conversation diet scale to estimate dietary intake behaviors in our participants.
4. **Physical Activity:** We will use the International Physical Activity Questionnaire (IPAQ) short version to assess the frequency and duration of various physical activities undertaken by adults over the past 7 days. This scale will provide an estimate of the number of minutes per week participants engage in each category of physical activity (e.g., vigorous, moderate, and mild intensity).
5. **Medication Taking:** We will use the Adherence to Refills and Medications Scale (ARMS) to assess adherence to medication-taking at baseline, 6, and 12 months.

**Covariates: Sociodemographic, health characteristics, acculturation, and SDOH.** We will use a sociodemographic and health questionnaire to collect basic information about the participant such as age, gender, education, income, duration of residence in the US, English proficiency, diabetes medication regimen, duration of T2D, and medical history. We will also use the PINE Study Acculturation Scale to evaluate various levels of acculturation in the sample and adjust for this in the statistical models if needed. This scale has established reliability and validity in Chinese immigrants. We will use the Social Determinants of Health (Core) survey from the NIH PhenX Toolkit to assess SDOH in Chinese immigrants.

#### **4.6 Payments**

The study will include 3 telephone surveys, baseline, 6, and 12 months. Patients will be paid \$30 by Clincard which will be mailed to them for each survey. If participants finished all three surveys, they will receive a total of \$90 in Clincard. We will also provide patients with an additional \$20 at baseline, 6 months, and 12 months for completing the A1CNow Self Check test, totaling \$60. In total, patients will receive up to \$150 for completing the study.

### **Aim 4 Implementation Evaluation**

**4.7 Evaluation Framework.** We will utilize the RE-AIM framework to evaluate the impact of the proposed intervention. We will also use CFIR framework to evaluate facilitators and barriers to the implementation process (See **Table 2**).

**Table 2: RE-AIM and CFIR Evaluation Frameworks**

| CONSTRUCTS                                                                                                                                   | MEASURES (Quantitative/Qualitative)                                                                                                                                                                                               | DATA SOURCES                                                                                                    | TIME FRAME                                                                      |
|----------------------------------------------------------------------------------------------------------------------------------------------|-----------------------------------------------------------------------------------------------------------------------------------------------------------------------------------------------------------------------------------|-----------------------------------------------------------------------------------------------------------------|---------------------------------------------------------------------------------|
| REACH: What % of the target population came into contact with the program? Were participants representative of the target population? |                                                                                                                                                                                                                                   |                                                                                                                 |                                                                                 |
| Participants                                                                                                                                 | 
 
% patients with uncontrolled T2D
 
% patients at risk who received the VIDEO+CHW intervention
 
Representativeness of patients referred and participated in study
 
 | 
 
EHR data
 
In-depth interviews with providers and CHWs
 
 | 
 
Baseline, 6 months, 12 months
 
 |
| EFFECTIVENESS: Did program achieve key targeted outcomes? Did it produce any unintended adverse consequences?                         |                                                                                                                                                                                                                                   |                                                                                                                 |                                                                                 |

|                                                                                                                                                                                                                                                                                                                                                                     |                                                                                                                                                                                                                                                                                                     |                                                                                                                                                                                                                                             |                                                                                                                                                                                               |                                                                   |
|---------------------------------------------------------------------------------------------------------------------------------------------------------------------------------------------------------------------------------------------------------------------------------------------------------------------------------------------------------------------|-----------------------------------------------------------------------------------------------------------------------------------------------------------------------------------------------------------------------------------------------------------------------------------------------------|---------------------------------------------------------------------------------------------------------------------------------------------------------------------------------------------------------------------------------------------|-----------------------------------------------------------------------------------------------------------------------------------------------------------------------------------------------|-------------------------------------------------------------------|
| Primary Outcome                                                                                                                                                                                                                                                                                                                                                     | • Change in HbA1c at 6 months                                                                                                                                                                                                                                                                       | • Patient data from EHR                                                                                                                                                                                                                     | • Baseline, 6 months, 12 months                                                                                                                                                               |                                                                   |
| Secondary Outcomes                                                                                                                                                                                                                                                                                                                                                  | • Change in HbA1c at 12 months and changes in self-efficacy,  diabetes self-management behaviors,  dietary intake,  physical activity,  medication adherence,  and SDOH  (at 6 and 12 months) | • Patient data from EHR
• Patient survey
• Healthify referrals                                                                                                                                                                        | • Baseline, 6 months, 12 months                                                                                                                                                               |                                                                   |
| ADOPTION: Did the organization use the program?                                                                                                                                                                                                                                                                                                              |                                                                                                                                                                                                                                                                                                     |                                                                                                                                                                                                                                             |                                                                                                                                                                                               |                                                                   |
| Adoption                                                                                                                                                                                                                                                                                                                                                            | • Utilization patterns                                                                                                                                                                                                                                                                              | a) Provider, CBO, CHW interviews
b) Utilization reports (Redcap)
c) % of DSMES videos being watched; # of CHWs calls and duration of the call (Redcap)                                                                                | a) Baseline, 12 months
b,c) Weekly                                                                                                                                                         |                                                                   |
| IMPLEMENTATION (CFIR constructs to systematically guide identifying barriers/facilitators to implementation): How closely did staff members follow the program (consistency of delivery)? How well did the staff adhere to intervention fidelity? Was the program delivered as intended? Was the program consistent and aligned with clinic sites' missions? |                                                                                                                                                                                                                                                                                                     |                                                                                                                                                                                                                                             |                                                                                                                                                                                               |                                                                   |
| CFIR                                                                                                                                                                                                                                                                                                                                                         | Intervention Characteristics/

Fidelity                                                                                                                                                                                                                                                       | a) % of staff attending trainings and orientations; utilization patterns
b) # DSMES videos watched by the patient
c) # CHW phone calls attended per patient and fidelity to the protocol
d) Utilization patterns of CHW case notes | a) Training log, trainee evaluations; Utilization reports (Redcap)
b) Video watch records (Redcap)
c) Fidelity checklist, CHW encounter logs (Redcap)
d) Redcap utilization records; | a) Baseline; Post training; 6 months
b,c) Monthly
d) Weekly |
|                                                                                                                                                                                                                                                                                                                                                                     | Characteristics of Individuals                                                                                                                                                                                                                                                                      | • Attitudes, norms, self-efficacy, and intention                                                                                                                                                                          | • Provider surveys                                                                                                                                                                            | • Baseline, 12 months                                             |
|                                                                                                                                                                                                                                                                                                                                                                     | Inner Setting                                                                                                                                                                                                                                                                                       | • Barriers and facilitators to workflow and referral processes                                                                                                                                                                              | • Provider, CBO, CHW interviews/surveys                                                                                                                                                       | • 12 months                                                       |
|                                                                                                                                                                                                                                                                                                                                                                     | Outer Setting                                                                                                                                                                                                                                                                                       | • Perceived contextual barriers and facilitators                                                                                                                                                                                            | • Provider, CBO, CHW interviews                                                                                                                                                               | • 12 months                                                       |
| MAINTENANCE: Is the organization willing to sustain the program? Is the program able to become part of routine practice?                                                                                                                                                                                                                                     |                                                                                                                                                                                                                                                                                                     |                                                                                                                                                                                                                                             |                                                                                                                                                                                               |                                                                   |
| Practice patterns                                                                                                                                                                                                                                                                                                                                                   | • Current site patterns, barriers and facilitators                                                                                                                                                                                                                                                  | • Provider, CBO, and CHW interviews                                                                                                                                                                                                         | • 12 months                                                                                                                                                                                   |                                                                   |
| Organizational characteristics                                                                                                                                                                                                                                                                                                                                      | • # patients, FTEs, staff characteristics                                                                                                                                                                                                                                                           | • Baseline surveys with sites                                                                                                                                                                                                               | • Baseline                                                                                                                                                                                    |                                                                   |

**D4.2. Data Sources and Collection:** 1) To capture data on *utilization patterns* of the intervention, we will extract system files from the RedCap databases every week that have date and time stamps and user logins to assess participation and completion of intervention components. Data will be extracted and analyzed by the NYU research team. 2) At baseline and follow-up, study coordinator will administer *brief surveys* to participating physicians (n=10) to capture data on: satisfaction with workflow before and after intervention, information sources before and after intervention, acceptability of and satisfaction with the integrated intervention, and barriers and facilitators of care coordination tools, building on our prior work. 3) Study coordinator will conduct *qualitative key informant interviews* with physician champion and/or administrators at CBWCHC, community organizations that serve as referral sites, and CHWs (n=15). At baseline, interviews will assess current satisfaction and usage CHW and organizational workflows. At follow-up, the interviews will assess barriers and facilitators to the implementation and adoption process of the integrated intervention, appropriateness, fidelity to the interventions, and to solicit recommendations for the replication and scalability of the intervention to other sites. We will also assess satisfaction and outcomes from the partnership and capacity building process. Questions will be adapted from existing validated measures on acceptability, feasibility, adoption, organizational culture, and scalability and our previous work. 4) We will conduct *fidelity checklists* during CHW biweekly phone calls for the first 2 months to assess that CHWs are covering all the key points outlined in the protocol. A kappa fidelity score will be calculated based on the percentage of key points completed, and provided to the study team. If CHW cannot improve fidelity to > 80% after two months, he/she will not be retained. In addition, CHWs will

keep encounter logs of all interaction with study participants and materials will be reviewed monthly by the study coordinator.

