**Analytic Plan for Aim 4.** Utilizing the RE-AIM framework, we will address “reach” by comparing demographic and clinical characteristics of patients enrolled vs. eligible and not enrolled, using Wilcoxon’s rank-sum test or Fisher’s exact test. We will also examine these factors separately by sex and age brackets. To address “effectiveness”, we will use the random linear mixed modeling to examine whether the VIDEO+CHW intervention group had a greater reduction than the CONTROL group. For “adoption”, we will use Chi-square tests to compare the proportion of patients completing intervention components. To address “implementation”, we will report the frequency of barriers/facilitators to implementation, as well as other fidelity measures, and Chi-

square tests to compare proportions. Finally, both “implementation” and “maintenance” will be explored qualitatively as described below.

Barriers and facilitators to implementation of the VIDEO+CHW intervention. All interviews will be audio-recorded and transcribed. We will use “constant comparison” analytic approach. The “constant comparison” approach is a method of explanation building in which the findings of an initial case are compared to a provisional category, revised as necessary and then other details or new cases are then compared against the revision and revised again as needed. This process is continued until an area of interest is fully explicated, reaching theoretical saturation. Using “thematic” coding, we will develop an initial set of codes, which will be reviewed by the Steering Committee to ensure they are relevant and complete. For each core code, we will ultimately develop one or more “secondary codes” that represent either more specific or restricted aspects of the phenomenon, to contextualize it, or to suggest underlying meanings. The secondary codes will vary in specificity or subtlety depending on the judged substantive value of additional refinements. Transcripts will be coded by at least four coders (graduate and post-doctoral students). Discrepancies in coding will be discussed and resolved, then the process is repeated with a new set of transcripts until an acceptable level of inter-coder reliability between them has been achieved, estimated using an appropriate chance-corrected statistic (e.g., kappa for nominal data and T-index for ordinal data). We will use Atlas.ti software to analyze the transcripts.

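### The study coordinator who reviews the CHWs' work each month also interviews them, so the CHW interview answers in Aim 4 may lean towards success

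*Protocol*

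**What the plan says.** Protocol section D4.2, which follows Table 2, assigns two tasks to one role.

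- **Oversight.** CHWs will "keep encounter logs of all interaction with study participants and materials will be reviewed monthly by the study coordinator".
- **Interviewing.** "Study coordinator will conduct *qualitative key informant interviews* with physician champion and/or administrators at CBWCHC", and the list of informants continues with "community organizations that serve as referral sites, and CHWs (n=15").

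On the content of the later round, D4.2 says: "At follow-up, the interviews will assess barriers and facilitators to the implementation and adoption process of the integrated intervention". The same sentence adds appropriateness and "fidelity to the interventions, and to solicit recommendations for the replication and scalability of the intervention to other sites". The baseline round covers current satisfaction and workflow instead.

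D4.2 also holds a staffing rule based on fidelity checklists from the CHW calls in the first two months: "If CHW cannot improve fidelity to > 80% after two months, he/she will not be retained". The checklist score goes to the study team. The rater is not identified, and neither is the person who decides on retention.

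Under the Aim 4 plan in section 7.1, "Transcripts will be coded by at least four coders (graduate and post-doctoral students").

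**The concern.** Someone asked about shortcomings in their own work by the person who checks that work has a reason to soften the answer. The expected direction is the same for every CHW: fewer barriers reported and delivery described as closer to protocol. More interviews would not average this out. The multiple coders and chance-corrected agreement in section 7.1 would not correct it either, because they address how a transcript is read and not what was left unsaid.

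Aim 4 (section 2.2) evaluates the VIDEO+CHW intervention, and CHWs deliver the component that sets it apart from VIDEO. Section 7.1 plans to report how often barriers and facilitators occur, and to explore implementation and maintenance qualitatively. Understated barriers in the CHW interviews would make the intervention look easier to deliver and replicate than it was.

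**Working it through.** No formula applies and the protocol states no figure to reproduce. The check is a comparison of who collects what, when, and for which construct.

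**1. Is it the same role?** Yes. D4.2 names the study coordinator both for the interviews and for the monthly review. The review sentence follows directly on the CHWs' logs, so the natural reading is that the logs are among the materials reviewed. No other interviewer for CHWs is named.

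**2. Do the interviews touch the reviewed work?** At follow-up, yes: fidelity and barriers are named topics. At baseline, much less so.

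**3. Which Aim 4 constructs use CHW interviews?** From Table 2:

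| Construct | CHW interviews a source? | Other sources listed | Timing |
|---|---|---|---|
| Reach | Yes | Provider interviews, EHR data | Baseline, 6, 12 months |
| Adoption | Yes | Provider and community-organization interviews; RedCap utilization, videos watched, number and length of CHW calls | Interviews at baseline and 12 months |
| Intervention characteristics and fidelity | No | Training records, watch records, fidelity checklist, encounter logs, RedCap use | Baseline to 6 months for training; otherwise monthly or weekly |
| Inner setting | Yes | Provider and community-organization interviews and surveys | 12 months |
| Outer setting | Yes | Provider and community-organization interviews | 12 months |
| Maintenance (practice patterns) | Yes | Provider and community-organization interviews | 12 months |

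Five constructs use CHW interviews, always alongside providers. The fidelity row does not use them. Section 4.4.2 adds a further check on delivery: CHW calls are audio recorded and a random selection is reviewed for adherence to protocol.

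**4. Does the retention rule bear on the interviews?** The rule looks at checklists from the first 2 months. Apart from reach, Table 2 places the follow-up CHW interviews at 12 months. For a CHW in post from the start, the gap is 12 − 2 = 10 months.

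**5. How many interviews are exposed?** The protocol does not give the number of CHWs, and the figure of 15 could mean CHWs alone or all informants. If it means all informants, and if there are 3 to 6 CHWs (an assumption with no source in the protocol), the share is 3/15 = 20% to 6/15 = 40%. If it means CHWs alone, all 15 CHW interviews are exposed. These shares count interviews held under the dual role. They do not count biased answers.

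**The case against.** The strongest case on the other side is that delivery is among the better-documented parts of Aim 4. Checklists, logs, watch records, call counts and sampled recordings do not depend on what a CHW says in an interview, and CHWs are never the only informants. Maintenance asks mainly whether the organization would continue, which is less exposed to a CHW's wish to look good. All of this stands and limits the point to the CHW interviews. It does not remove it: recordings and logs show what was done on calls but say little about why delivery was hard or what obstructed referral. Providers and community organizations can comment on these matters but do not make the calls.

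A reader might infer that the interviews take place under threat of dismissal, because the rule on fidelity above 80% is in the same paragraph. The documents do not support this. The rule is tied to early checklists, the coordinator is not named as rater or decision-maker, and nothing links interview answers to retention. Table 2 lists the checklist and logs as monthly, which makes continuing oversight plausible but does not extend the rule.

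A reader might also infer that Aim 4's findings on delivery will be biased as a whole. The table above shows otherwise, and even for the CHW interviews the documents show a risk and not a result.

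A last objection concerns the remedy. The student and post-doctoral researchers in section 7.1 are the transcript coders, and they may belong to the study team that receives the fidelity scores. Using one of them could mean coding one's own interviews, and would reduce the bias without abolishing it. This is fair, and the fix takes it into account.

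**Conclusion.** The dual role is written into D4.2 and is not merely a detail left open. Because of it, CHW interview answers on barriers, appropriateness and fidelity may be tilted towards success. The consequence is limited to the CHW-interview component of Aim 4, which feeds five constructs in Table 2 together with other sources. The quantitative fidelity measures, the provider and community-organization interviews, and HbA1c are unaffected.

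The size of any bias is unknown; the 20–40% share rests on an assumed number of CHWs and on reading 15 as all informants. The conclusion rests on two further assumptions: that the logs are part of the monthly review, and that the same coordinator does both jobs. The point is minor, but worth acting on because the remedy is so cheap.

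**What to change.** In D4.2, assign the CHW interviews to an existing team member who has no part in log review, fidelity scoring or CHW oversight. If one of the transcript coders in section 7.1 is used, state that this person does not code the interviews that he or she conducted. Add that identifiable CHW answers are not shared with those who oversee CHWs. The coordinator can keep the physician, administrator and community-organization interviews and the physician surveys.

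The cost is a short wording change, brief training for the new interviewer and, if a coder is used, some care in allocating transcripts. No sample size, endpoint or analysis changes.
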